### Randomization and blinding

2.3

The patients were enrolled by a dedicated surgeon on our team. For eligible patients treated with GC at The Fourth Hospital of Hebei Medical University, thoracoabdominal CT, echocardiography, ultrasound of supraclavicular LNs, sonography of lower extremity veins, electrocardiogram and lung function examination should be performed before the operation. The patients who meet the inclusion criteria and are feasible for radical onco-surgery are then randomized to receive either endoscopic injection of CNSI (CNSI group) or endoscopic injection of ICG (ICG group) during gastroscopy at a 1:1 ratio. Randomization has been achieved using a random number table by the data manager, and the allocation is not concealed. While the blinding of the surgeons or participants is impossible, the pathologists are blinded to the types of surgical approaches.

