**Figure 2 f2:**
[figure not shown]
Endoscopic injection of lymph node tracer. **(A)** Carbon nanoparticle suspension injection; **(B)** Indocyanine green.

For those who were randomly assigned to the ICG group, ICG (25 mg/dose) produced by Dandong Yichuang Pharmaceutical is marked in the endoscopy division 1 day before surgery and is injected submucosally at 4 points (proximal side, distal side, and left and right sides) 0.5-1 cm from the tumor edge under endoscopy. The optimized dose for each point is approximately 0.5 ml (**Figure 2B**).Both procedures are performed by a designated, experienced endoscopic specialist.

Laparoscopic exploration and detection of free peritoneal cancer cells are necessary in the first step of the surgical procedure to exclude adjacent organ infiltration and peritoneal metastasis. When the patient is positioned in the reverse Trendelenburg position (described as the foot-down and head-up supine position), 800 ml of normal saline is routinely used to wash the area near the carcinomatous foci of GC and is then re-collected as much as possible. It is important to collect at least 300 ml of the flushing fluid from the pelvic cavity. Cytology examination is then immediately performed on the flushing fluid collected. If the peritoneum is free of metastasis and peritoneal lavage cytology is negative, standard laparoscopic or robotic radical gastrectomy with D2 lymphadenectomy is then performed by the designated and experienced team of surgeons according to the Japanese Gastric Cancer Treatment Guidelines 2014. Distal gastrectomy for LN dissection included LN station 1, 3, 4 sb, 4d, 5, 6, 7, 8a, 9, 11p, 12a.

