Before starting to retrieve LNs from the GC patients, the surgeon should determine the positions of each station LN on the specimen in detail and plan the sequence of retrieving the LNs. After washing and flattening the specimen, we began to retain the soft tissues of each station of LNs by cutting off the useless tissues in the specimen (**Figure 3**). Then, after observing the course of the artery encased in fatty tissue and removing the perivascular fat, we dissected the LNs arranged along the vascular lumen. Dissecting the LNs must be completed within 30 minutes after the specimen is detached. The dissected LNs, which are fixed with formalin, were then separated by the different LN stations, the staining status and the LN maximum diameter (>2 or ≤2 mm) and sent to the pathology department for histopathological study. The surgeon appointed to the dissection of the LNs must have a thorough grasp of the knowledge about LNs and abundant experience.

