## Discussion

3

Despite the serious burden of GC in China, the public awareness of risk factors or warning symptoms and screening is low, and there is a lack of screening programs (20). Therefore, the majority of GC are detected at an advanced stage, and at this moment, LN metastasis usually occurs. It is well known that LN metastasis is one of the most important prognostic factors for GC patients, and D2 LN dissection has gradually become the mainstream treatment to improve patient outcome (21). The mean number of LNs dissected in Western European countries was 29.5, which is slightly higher than that in China (22). This condition might be associated with the insufficient LN dissection intraoperatively and the false idea that postoperative LN dissection should be completed by a pathologist. Currently, an increasing number of studies have begun to focus on LN tracers, and an increasing number of gastrointestinal surgeons have started using carbon nanoparticle suspension injection or indocyanine green.

A number of interesting differences were identified through our analyses of CNSI and ICG. First, taking an appropriate amount of time to dissect LNs as an example, the LNs are stained black using CNSI, while the LNs labeled with ICG have the ability to generate strong fluorescence emission in certain cases. When utilizing CNSI as a tracer of LNs, surgeons can dissect the LNs under direct vision without the assistance of other instruments. However, if surgeons intend to use indocyanine fluorescence imaging to guide the postoperative nodal dissection, the fluorescence imaging mode must be available, and the wear and tear of the instrument and the burden on surgeons and operating room nurses will increase, which may prolong the time needed for dissecting the LNs. Second, compared with CNSI, ICG may have the potential to decrease the risk of anastomotic fistula with the assistance of examining the blood supply of the anastomosis. Third, CNSI extravasation into gastric serosa will contaminate the surgical fields and increase the difficulty of surgically dissecting the gastric tumor, but surgeons can switch between the fluorescence mode and normal mode to avoid the adverse effects caused by ICG extravasation (15).

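### The stated pathologist blinding refers to surgical approach, and node handling does not establish masking to the randomized tracer or to stain status

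*Protocol article*

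**What the plan says.** Section 2.3 (Randomization and blinding) says that eligible patients are "randomized to receive either endoscopic injection of CNSI (CNSI group) or endoscopic injection of ICG (ICG group) during gastroscopy at a 1:1 ratio". It then makes the trial's one blinding statement: surgeons and participants cannot be blinded, but "the pathologists are blinded to the types of surgical approaches".

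Section 2.4 (Interventions) uses the language of operative approach when it says that "standard laparoscopic or robotic radical gastrectomy with D2 lymphadenectomy is then performed". It also describes specimen handling. An appointed surgeon dissects the nodes from the specimen. The fixed nodes "were then separated by the different LN stations, the staining status and the LN maximum diameter" and are "sent to the pathology department for histopathological study".

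On how the tracers look, the Discussion says that "the LNs are stained black using CNSI, while the LNs labeled with ICG have the ability to generate strong fluorescence emission". It adds that CNSI nodes can be dissected by eye without other instruments. The Introduction also describes CNSI as black and strongly colouring.

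Section 2.5 (Outcomes) makes the number of retrieved nodes primary. It lists several stain-by-metastasis rates, the metastasis rate and the number of metastatic nodes as secondary. Section 2.8 takes the data from pathology and operative reports.

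**The concern.** In an open-label trial whose allocation is stated not to be concealed, the pathology reading is the one assessment presented as blinded. The sentence names a factor that the trial does not compare, and the handling procedure passes the stain classification along with the nodes.

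This matters because four of the secondary rates cross stain status with metastatic status. In those rates the stain is the test and histology is the reference standard. A reader who knows the stain status, or can see it, is reading the reference standard with knowledge of the test result. A trial report that simply called the pathologists blinded would claim more protection for these outcomes than the article describes.

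**Working it through.** No arithmetic applies: the point depends on no sample size, error rate or standard deviation. The check sets the sections side by side.

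**Step 1. What is randomized?** The tracer (Section 2.3).

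**Step 2. What does the blinding sentence cover, read literally?** Types of surgical approach. The only approaches named are laparoscopic and robotic (Section 2.4), and patients are not randomized between them. On this reading the sentence may be true, but it says nothing about the tracer.

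**Step 3. What if the phrase loosely means the tracer group?** Then it has to be squared with three statements:
- Nodes are sorted by staining status before they go to pathology (Section 2.4).
- CNSI nodes are black to the eye (Introduction, Discussion).
- ICG nodes are recognised by fluorescence (Discussion).

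In a two-arm trial, a stained group that is black points to CNSI, and a stained group that is not black points to ICG. No step that hides the sorting or the colour is described. This is an inference from the three statements, though a short one.

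**Step 4. Which outcomes depend on the pathologist?** From the definitions in Section 2.5 and the procedure in Section 2.4:

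| Outcome | What sets it | Needs metastatic status? |
|---|---|---|
| Number of nodes retrieved (primary) | Unblinded surgeon's dissection | No |
| Staining rate, overall and per station | Unblinded surgeon's retrieval and sorting | No |
| Stained positive, stained negative, nonstained positive and nonstained negative rates | Sorting, then histology | Yes |
| Metastasis rate | Retrieval, then histology | Yes |
| Number of metastatic nodes | Retrieval, then histology | Yes |

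So 4 + 1 + 1 = 6 secondary outcomes are exposed. The four rates form two complementary pairs: stained and nonstained positive rates share the denominator of all positive nodes and sum to 1, and the two negative rates likewise share the denominator of all negative nodes. They therefore carry two separate quantities, the stained share of positive nodes and the stained share of negative nodes.

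**Step 5. Can a bias be sized?** No. The article gives nothing on how often reading with knowledge of the stain would change a node's classification, or in which direction.

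**The case against.** The strongest reply has four parts.

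- **The trial is openly unblinded.** It calls itself open-label, and on the literal reading the sentence is not contradicted. This is true. But a blinding statement that omits the randomized factor gives no protection for the comparison, and readers are likely to take it as if it did.
- **Sorting is not disclosure.** Nodes must be separated by stain to compute the planned rates, and the article does not say how containers are labelled. Coding could be described in a full protocol. This stands as a limit: it cannot be asserted that pathologists know the arm. It does not answer the colour of CNSI nodes, which coding would not hide.
- **The surgeon is the main source of risk.** The surgeon finds, counts and sorts the nodes, unblinded. This stands in full. A reader might infer that the pathology problem threatens the primary outcome, or every node outcome, through the pathologist's search effort. The article does not support that: Section 2.4 gives the search to the surgeon, so pathologist blinding would not protect the retrieval count or the staining rates even if it were perfect.
- **No effect is shown.** A reader might also try to turn the point into an inflated false-positive rate for the primary comparison. That would need a standard deviation, which Section 2.7 does not give, and a bias in nodes, which would have to be invented. No such figure belongs here.

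**Conclusion.** The point holds in limited form. The blinding sentence does not establish that pathologists are masked to the tracer or to stain status: literally it concerns a different factor, and loosely it sits badly with the article's own specimen handling and its description of CNSI.

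The consequence is confined to the six secondary outcomes that rest on histological metastatic status. The primary count and the staining rates are outside the point. No size or direction of bias can be given.

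The conclusion assumes that the sorting remains apparent when the nodes arrive, or that CNSI pigment is visible to the pathologist. Both are reasonable inferences, and neither is stated. It would be wrong to write as fact that the pathologists know the arm. The correction is worth making and needs no redesign.

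**What to change.** **Specimens still to be processed.** Label containers with a code and the station only. Keep the key linking codes to stain status with the data manager, and merge it after the pathology report is signed.

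**Wording of Section 2.3.** Replace the clause on pathologists with: pathologists are not told the tracer or the stain status, but CNSI pigment may be visible, so assessment is not fully blind to the tracer.

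**Specimens already processed without coding.** State that pathology assessment was not blinded to the tracer. This may be the case that mainly applies: the Abstract speaks of 96 patients enrolled in the past tense, and Section 2.7 plans one year of recruitment from a start in January 2021 (Section 2.1).

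**Cost.** Container relabelling, a key to hold, and a corrected sentence; no extra reader. The limit is that coding can hide the stain label for ICG nodes but masks CNSI nodes only partly, because their colour remains. The change does nothing for the outcomes set by the surgeon and should not be presented as if it did.

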### Interventions

2.4

In the CNSI group, the patients are given injections of CNSI (50 mg/dose) produced by Chongqing Lummy Pharmaceutical Co., Ltd. in the endoscopy division 1 day before surgery. CNSI is injected submucosally at 4 points (proximal side, distal side, and left and right sides) 0.5-1 cm from the tumor edge under endoscopy. The optimized dose for each point is approximately 0.25 ml (**Figure 2A**).

**Figure 2 f2:**
[figure not shown]
Endoscopic injection of lymph node tracer. **(A)** Carbon nanoparticle suspension injection; **(B)** Indocyanine green.

For those who were randomly assigned to the ICG group, ICG (25 mg/dose) produced by Dandong Yichuang Pharmaceutical is marked in the endoscopy division 1 day before surgery and is injected submucosally at 4 points (proximal side, distal side, and left and right sides) 0.5-1 cm from the tumor edge under endoscopy. The optimized dose for each point is approximately 0.5 ml (**Figure 2B**).Both procedures are performed by a designated, experienced endoscopic specialist.

Laparoscopic exploration and detection of free peritoneal cancer cells are necessary in the first step of the surgical procedure to exclude adjacent organ infiltration and peritoneal metastasis. When the patient is positioned in the reverse Trendelenburg position (described as the foot-down and head-up supine position), 800 ml of normal saline is routinely used to wash the area near the carcinomatous foci of GC and is then re-collected as much as possible. It is important to collect at least 300 ml of the flushing fluid from the pelvic cavity. Cytology examination is then immediately performed on the flushing fluid collected. If the peritoneum is free of metastasis and peritoneal lavage cytology is negative, standard laparoscopic or robotic radical gastrectomy with D2 lymphadenectomy is then performed by the designated and experienced team of surgeons according to the Japanese Gastric Cancer Treatment Guidelines 2014. Distal gastrectomy for LN dissection included LN station 1, 3, 4 sb, 4d, 5, 6, 7, 8a, 9, 11p, 12a.

Before starting to retrieve LNs from the GC patients, the surgeon should determine the positions of each station LN on the specimen in detail and plan the sequence of retrieving the LNs. After washing and flattening the specimen, we began to retain the soft tissues of each station of LNs by cutting off the useless tissues in the specimen (**Figure 3**). Then, after observing the course of the artery encased in fatty tissue and removing the perivascular fat, we dissected the LNs arranged along the vascular lumen. Dissecting the LNs must be completed within 30 minutes after the specimen is detached. The dissected LNs, which are fixed with formalin, were then separated by the different LN stations, the staining status and the LN maximum diameter (>2 or ≤2 mm) and sent to the pathology department for histopathological study. The surgeon appointed to the dissection of the LNs must have a thorough grasp of the knowledge about LNs and abundant experience.

**Figure 3 f3:**
[figure not shown]
The lymph nodes after dissecting the lymph nodes from specimen.

### Outcomes

2.5

The primary outcome of this study is to determine the number of LNs retrieved. The secondary outcomes are to determine the LN staining (or fluorescence) rate (Number of staining or fluorescence LNs/Total number of retrieved LNs), LN staining (or fluorescence) rate at each station, stained (or fluorescent) LN positive rate(Number of staining or fluorescence positive LNs/Total number of positive LNs), stained (or fluorescent) LN negative rate(Number of staining or fluorescence negative LNs/Total number of negative LNs), nonstained (or nonfluorescent) LN positive rate(Number of nonstaining or nonfluorescence positive LNs/Total number of positive LNs), nonstained (or nonfluorescent) LN negative rate(Number of nonstaining or nonfluorescence negative LNs/Total number of negative LNs), LN metastasis rate(Number of metastasis LNs/Total number of retrieved LNs), number of metastatic LNs, complication and mortality rates within 30 days, 3-year disease-free survival (DFS), 3-year overall survival (OS), recurrence pattern within 3 years, intraoperative blood loss volume, time spent retrieving LNs, and postoperative recovery (exhaust time after surgery, feeding time after surgery, duration of postoperative hospital stay).

Any complications should be recorded and reported. There are mainly two complications related to the procedure: intraoperative complications and postoperative complications. The former includes bleeding, injuring the viscera, lymphatic leakage and so on. The latter should be classified according to the Clavien−Dindo classification system.

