**Method/design:**

The FUTURE-01 trial will be the first randomized, open-label, single-center trial to compare CNSI and ICG. The study started in 2021 and enrolled 96 patients according to a prior sample size calculation. The primary outcome is the number of LNs retrieved. The secondary outcomes are LN staining rate, LN metastasis rate, stained LN metastasis rate, perioperative recovery and survival.

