### Eligibility criteria

2.2

The inclusion criteria are as follows: (1) aged 18–75; (2) histologically proven gastric adenocarcinoma on biopsy (papillary adenocarcinoma, tubular adenocarcinoma, mucous adenocarcinoma, signet-ring cell carcinoma or poorly differentiated adenocarcinoma); (3) proven clinical stage of cT1-4a N0/+ M0 by ultrasound endoscopy, enhanced CT/MRI examination or diagnostic laparoscopy according to the TNM classification of the American Joint Committee on Cancer (AJCC cancer staging manual, eighth edition); (4) without distant metastasis and no invasion of adjacent organs; (5) a preoperative Eastern Cooperative Oncology Group (ECOG) score of 0 or 1; (6) a preoperative American Society of Anesthesiologists (ASA) score of I-III; and (7) signed a written informed consent form.

The exclusion criteria are as follows: (1) pregnant or lactating women; (2) patients with severe mental disorder; (3) a history of upper abdominal surgery (with exception of laparoscopic cholecystectomy); (4) a history of gastrectomies, endoscopic mucosal resection (EMR) or endoscopic submucosal dissection (ESD); (5) enlarged or bulky regional LNs according to preoperative imaging and larger than 3 cm at the long diameter; (6) the tumor invades the duodenum or esophagus; (7) Borrmann type IV GC; (8) history of other malignant tumors within the last 5 years; (9) received previous neoadjuvant radiotherapy or chemotherapy; (10) history of myocardial infarction or unstable angina within the last 6 months; (11) history of cerebrovascular accident within the last 6 months; (12) undergoing sustained systemic corticosteroid treatment within 1 month prior to surgery; (13) emergency surgery due to GC complications (bleeding, perforation, or obstruction); and (14) FEV1 <50% predicted value.

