### Sample size

2.7

The sample size for this study was calculated based on previous research by our team and computed by PASS version 11. Eligible subjects were randomly assigned (1:1) into the CNSI group and the ICG group. All analyses were two-sided with α=0.05 and β=0.80. the prospective mean number of the LNs retrieved in the CNSI group was 56.93. The prospective mean number of the LNs retrieved in the ICG group was 50.52. The total sample size was 96 (48 per group) after taking into account a 10% dropout rate in each group. The planned recruitment period is 1 year, and the follow-up duration is 3 years.

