### Data collection and analysis

2.8

Designated and trained surgeons collect the data from the pathology reports and operative reports. The focus of the data should contain clear information about the tumor location, tumor size, histopathologic type, tumor differentiation degree, Lauren classification, vascular tumor embolus, nerve invasion, immunohistochemistry results and pathological findings of the LNs at each station. Long-term prognosis data are collected *via* follow-up up until 3 years after the surgical operations. The follow-up should consist of a 3-month interval from 0–2 years and a 6-month interval in the third year. The main follow-up items included routine physical examination, tumor marker detection (CEA, CA199, CA724 and AFP), abdominal CT, and annual electronic gastroscopy. The follow-up included an outpatient follow-up, a telephone follow-up and a short message platform follow-up. Further evaluation and treatment should be performed if relapse occurs.

The purpose of this study is to compare the safety and efficacy of CNSI and ICG during radical gastrectomy. The primary objective is to determine the number of LNs retrieved. Comparability analysis will be performed on the baseline data to determine whether the two groups are comparable. The number of patients, mean, standard deviation, median, maximum, and minimum will be listed. Descriptive data will be presented as the mean ± SD, while categorical data will be presented as the number and percentage (%). The independent samples t test or nonparametric test will be used to analyze continuous data, and the chi-square test or Fisher’s exact test will be used to analyze categorical variables. It is valuable to analyze the influence of CNSI (ICG) staining or other factors on the number of LNs detected according to the statistical analysis. We can also research the effect of CNSI (ICG) staining on the operative time, intraoperative bleeding volume, intraoperative transfusion volume and postoperative complications. Survival analysis will be performed using the Kaplan−Meier method, and the log rank test will be used to test the difference in survival rates between the two groups. SPSS 26.0 statistical software will be used for statistical analysis. P<0.05 will be considered to indicate statistically significant differences.

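### Section 2.8 does not fix the unit of analysis for the node-level secondary rates; a chi-square test on pooled nodes would ignore within-patient correlation and inflate the type I error

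*Protocol article*

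**What the plan says.** Section 2.5 (Outcomes) lists several secondary outcomes as one node count divided by another. The overall staining rate is "LN staining (or fluorescence) rate (Number of staining or fluorescence LNs/Total number of retrieved LNs"; the same rate is also wanted at each station. The LN metastasis rate likewise divides by all retrieved nodes. Four further rates cross staining with pathology, for example "nonstained (or nonfluorescent) LN positive rate(Number of nonstaining or nonfluorescence positive LNs/Total number of positive LNs". The abstract puts rates of this kind first: "The secondary outcomes are LN staining rate, LN metastasis rate, stained LN metastasis rate".

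Section 2.8 (Data collection and analysis) gives general test rules. Continuous data get an independent-samples t test or a nonparametric test. Categorical data are reported as number and percentage, and a chi-square or Fisher's "exact test will be used to analyze categorical variables". The threshold is "P<0.05 will be considered to indicate statistically significant differences". No test is tied to any node rate, the unit (patient or node) is not named, and no method for correlated observations is mentioned.

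Patients are the randomised unit (Sections 2.3 and 2.7). Each patient has one tumour and one tracer injection session (Section 2.4).

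**The concern.** Staining and metastasis are yes/no facts about a single node. An analyst who takes a stained count over a total count, and a rule that sends categories to chi-square, can easily build a two-by-two table of nodes by arm. That table would hold about 2,170 to 2,450 nodes per arm from only about 43 patients. Nodes from one patient share the injection, the tumour, the surgeon's dissection and the pathology, so their results are correlated. The chi-square test ignores this, and its standard error is too small.

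These rates are the direct comparison of how well the two tracers mark nodes. An apparent staining difference with a small p-value could be no more than variation between patients.

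**Working it through.** **Inputs from the documents**
- Expected nodes per patient (Section 2.7): "the prospective mean number of the LNs retrieved in the CNSI group was 56.93", and 50.52 in the ICG group. Average m = (56.93 + 50.52)/2 = 53.7.
- 48 patients per arm with 10% dropout (Section 2.7): 48 × 0.9 = 43.2, so about 43 evaluable per arm.
- Nodes per arm: 43 × 50.52 = 2,172 and 43 × 56.93 = 2,448.
- Two-sided test at 0.05.

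The plan states no figure for the node-level rates, so there is none to reproduce. Its sample size concerns the primary outcome and does not bear on this point.

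**Assumption.** The documents give no ICC for nodes within a patient. The range 0.02 to 0.20 is assumed.

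**Formulas**
- Design effect: D = 1 + (m − 1) × ICC.
- True error of a nominal 5% test that ignores clustering: 2 × [1 − Φ(1.96/√D)].

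**Rates over all retrieved nodes (m = 53.7)**

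| Assumed ICC | D | True error, formula | True error, simulation |
|---|---|---|---|
| 0.02 | 1 + 52.7 × 0.02 = 2.05 | 0.17 | 0.17–0.18 |
| 0.05 | 1 + 52.7 × 0.05 = 3.64 | 0.30 | 0.31 |
| 0.10 | 1 + 52.7 × 0.10 = 6.27 | 0.43 | 0.44 |
| 0.20 | 1 + 52.7 × 0.20 = 11.55 | 0.56 | 0.57 |

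The simulation drew beta-binomial data with no true difference: 43 patients per arm, 10,000 runs, true rates of 0.2 and 0.6, and an assumed SD of 10.6 for the node count. With almost no correlation (ICC 0.0001) the pooled test was sound, at 0.052 to 0.053. In the same simulated data, a t test on per-patient proportions rejected in 0.048 to 0.054 of runs.

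**Rates with smaller denominators**
- Positive-node rates: the cluster is a patient's positive nodes only. Assuming 3 per patient, D is 1.10 to 1.40 over ICC 0.05 to 0.20, and the error is 0.06 to 0.10. Assuming 8, D is 1.35 to 2.40 and the error is 0.09 to 0.21.
- Negative-node rates: with 8 positive nodes removed, about 46 remain. The error is 0.28 at ICC 0.05 and 0.54 at ICC 0.20, close to the figures for all nodes.
- Per-station rates: Section 2.4 lists 11 stations for distal gastrectomy, and 53.7/11 is about 5 nodes per station by simple division. At m = 5 the error is 0.07 to 0.14 for ICC 0.05 to 0.20.

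**Complements.** The stained and nonstained positive rates share one denominator, all positive nodes, so they sum to 1. The stained and nonstained negative rates share all negative nodes and also sum to 1. The four rates therefore give two distinct comparisons.

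**The case against.** A reader might infer that the protocol commits to pooling nodes and testing them by chi-square. It does not. The ratio can equally be formed for each patient, and a per-patient proportion is continuous, so Section 2.8 would send it to a t or nonparametric test. That reading fits the randomised unit and keeps the error near 5%. The unit of analysis might also be settled in an analysis plan that is not shown, and silence in a condensed article is not in itself an error. All of this stands, so the inflation is conditional on the reading and on an assumed ICC. What survives is that the article does state its list of tests. Read literally, that list lets a categorical node result go to a test that can give a wrong p-value.

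Three other strong readings are not supported.
- **The figures for about 54 nodes apply to every node rate.** They do not: positive-node and per-station clusters are much smaller.
- **Per-patient analysis fails for the positive-node rates.** Eligibility covers "proven clinical stage of cT1-4a N0/+ M0", so some patients may well have no positive node and hence a zero denominator. But a clustered analysis of positive nodes leaves out the same patients. A stated rule is needed; neither approach is ruled out.
- **The rates are the wrong ones, or contradict the abstract.** The defined rates are of the sensitivity and specificity type, a legitimate choice. Predictive values would be a preference, and they come from the same counts. The abstract gives no formula for its stained LN metastasis rate, so no conflict can be shown.

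**Conclusion.** The concern holds conditionally. The article leaves open whether node-level rates are analysed per patient or pooled, and it lists no method that allows for correlation among a patient's nodes. On the pooled chi-square reading, the true error for rates over all retrieved nodes is roughly 3 to 11 times the nominal 5% (0.17/0.05 = 3.4; 0.56/0.05 = 11.3) over the assumed ICC range 0.02 to 0.20. For positive-node rates it is about 1 to 4 times nominal (0.06/0.05 = 1.2; 0.21/0.05 = 4.2) under the stated assumptions. On the per-patient reading there is no material inflation.

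Only secondary outcomes are affected. The complementary rates are a minor matter: they make no result wrong, but each pair is one comparison and should be counted once.

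**What to change.** In Section 2.8, state three things:
- All node-level rates, including those at each station, are compared between arms with the patient as the cluster, by a binomial GEE with robust standard errors or a beta-binomial model.
- Patients without positive nodes contribute nothing to the positive-node rates, and the number of contributing patients is reported for each rate.
- Chi-square and Fisher's exact tests are used only for patient-level categorical variables, such as occurrence of a complication.

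In Section 2.5, note that the nonstained positive and nonstained negative rates are complements of the stained ones and are not separate comparisons.

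This changes wording and code only; nodes are already sorted by station and staining status before pathology (Section 2.4). A GEE with an independence working correlation still gives the pooled ratio in each arm as its estimate, so only the uncertainty changes. The cost is wider confidence intervals than a pooled analysis would show. For rates over all retrieved nodes the factor is √D: 1.4, 1.9, 2.5 and 3.4 at ICC 0.02, 0.05, 0.10 and 0.20.
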